## Intervention: the OPEN AOS model

The OPEN AOS model provides emergency substitution care to older adults residing in RACFs located within the MNHHS catchment area. Nurse-led and physician supported, OPEN AOS commenced in January 2022 and became fully operational by June 2022. The service is based in office space adjacent to a MNHHS hospital and operates 12 h per day between the hours of 08:00–20:00, Monday to Sunday. The service aims to (i) decrease the time to treating emergency clinician and (ii) reduce the number of avoidable ambulance transports to ED for older adults living in RACFs. The OPEN AOS model is staffed by 3.0 full-time equivalent (FTE) Nurse Practitioners^1^ (NP); 1.0 FTE NP candidates (NPC)^2^; and 1.8 FTE RNs^3^ [40, 41]. The model is supported by 1.4 FTE Senior Medical Officers (SMO)^4^ [42, 43] and 0.8 FTE Senior Pharmacists 5 [44]. The service is funded by MNHHS. Detailed descriptions of the responsibilities of the OPEN AOS clinical roles are provided in Additional file 1.

Patients of OPEN AOS are older adults residing in RACFs experiencing acute illnesses or injuries. OPEN AOS clinicians provide emergency substitution care via telehealth or in person. Referrals originate from the ambulance service (either from paramedics attending the patient at the RACF or following secondary telephone triage by experienced ambulance service clinicians), General Practitioners (GPs), RACF staff and other local teams providing specialist sub-acute RACF consulting services. Each referral is reviewed by an OPEN AOS clinician who triages the case and determines suitability for OPEN AOS care. Patients not meeting eligibility criteria for the OPEN AOS remain in the care of ambulance services for secondary triage and receive standard clinical review, consideration of referral pathways and standard ambulance attendance.

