## Study design

This pragmatic multi-methods study comprises three discrete but related components: concurrent retrospective quantitative data collection for Components 1 and 2, and prospective qualitative data collection for Component 3. The approach to quantitative and qualitative data collection enables a comprehensive examination of the model’s effectiveness and real-world application. Given the multi-methods design, integration of quantitative and qualitative data through triangulation will not be undertaken. The design is underpinned by the integrated Practical, Robust, Implementation and Sustainability Model (PRISM) and Reach, Effectiveness, Adoption, Implementation and Maintenance (RE-AIM) framework [45]. PRISM will support the identification and description of contextual factors impacting RE-AIM outcomes [45]. This study has been reviewed and approved by the Metro North Human Research Ethics Committee (HREC) B (ECOO168), approval number 102,923. Data storage, retention and disposal will be conducted in accordance with the National Health and Medical Research Council (NHMRC) guidelines [46].

Three components are planned to address the following research questions:

*Component 1*

To what extent (if any) do patient characteristics (such as age, sex, and diagnostic classification^6^) and outcomes differ between OPEN AOS care and standard care (i.e. ambulance attendance with transport to ED care)?Specifically:

4.Primary Outcome: Time to be seen by treating clinician, defined as the amount of time in minutes from the initial contact with QAS to the time seen by either (i) the OPEN AOS clinician (intervention group) or (ii) the ED medical officer (control group).5.Secondary Outcomes:6.Length of care episode, defined as the amount of time in hours from initial contact with QAS to discharge of care.7.Ambulance transport to ED care: defined as the proportion of OPEN AOS patients requiring transport to ED for definitive care.8.ED re-presentation for any cause within 48 h and 28 days of discharge.9.Death within 48 h of discharge.10.Clinical incident^7^ [47] data, defined as clinical incidents that are reported by MNHHS staff that occur within 48 h of discharge.

*Component 2*

Compared to standard care, what is the incremental cost (saving) per person of the OPEN AOS model? 

*Component 3*

How do contextual factors influence implementation and potential future scale and spread of the OPEN AOS model?

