### Inclusion criteria

Intervention: Adults aged 65 years or older who are permanent residents of RACFs situated within the MNHHS district geographical catchment area, with acute care needs and who were referred by the ambulance service to OPEN AOS between 08:00 and 20:00, Monday to Sunday, from 1 July 2022 to 30 June 2023. Patients can receive treatment by OPEN AOS on more than one occasion within the study period.

Control: Adults aged 65 years or older who are permanent residents of RACFs situated within the MNHHS district geographical catchment area, who received standard ambulance attendance and transport to a MNHHS ED between 08:00 and 20:00, Monday to Sunday, from 1 July 2022 to 30 June 2023. Only the first presentation for each patient within the study period will be examined.

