### Exclusion criteria

Patients were excluded if they (1) were assigned emergency status at primary (or secondary) triage (for any clinical reason); (2) did not reside in an RACF or resided in respite care; (3) were attended by ambulance and transported to ED care outside of OPEN AOS model operational hours (i.e. before 08:00 or after 20:00 Monday to Sunday); (4) were referred to OPEN AOS by any referrer other than ambulance services; or (5) received care outside the designated study period (1 July 2022 to 30 June 2023). (6) Patients included in the intervention group, i.e. those seen by OPEN AOS will be excluded from the control group.

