### Data analysis

For our analysis, the comparison of interest is between the intervention and control groups. Re-presentations by patients in either group are not considered as independent events and will be excluded from analyses, however the number of re-presentations during the study period will be noted for the OPEN AOS group. Categorical data will be presented as frequency and percentages, while continuous data will be reported as mean with standard deviation or median with interquartile ranges, depending on the distribution of the data. Categorical data will be analysed using the Pearson Chi-squared test or Fisher’s exact test, and continuous variables using the Student t-test or Mann-Whitney U test. Time to treating emergency clinician and time to discharge from the episode of care will be examined using a generalised linear model or parametric regression model if events are censored e.g., death of a patient. ED re-presentation and mortality will be examined using logistic regression if there are sufficient events. All regression models will be multivariable with fixed effects for triage score, weekend presentation, season, and ambulance referral time. The inclusion of Charlson Comorbidity Index [52] in regression analyses will depend on the extent of missing data. Component 1 will be reported in accordance with the Enhancing the QUAlity and Transparency Of health Research (EQUATOR) guidelines for reporting non-randomised studies [53].

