### Component 2: health economic evaluation

Component 2 will use a decision analytic model to estimate the cost-efficiency of the OPEN AOS model intervention with standard care, taking into consideration the subsequent probability of presentation and re-presentation to the ED. The perspective for the analysis will be from the public hospital and health system.

This economic evaluation will be undertaken using retrospective data collected concurrently with Component 1, drawing on the same sample, time periods, and a sub-set of the routinely collected de-identified and linked data. The primary outcome will be the incremental expected cost per patient treated via OPEN AOS compared to standard care. Component 2 will follow the Consolidated Health Economic Evaluation Reporting Standards 2022 [54].Total annual cost of the OPEN AOS and additional ED equivalent capacity created will be based on forecast annual utilisation of OPEN AOS derived from historic utilisation estimates. An estimate of the net monetary benefit of the OPEN AOS model will be derived based on the annual utilisation of the OPEN AOS model multiplied by the incremental expected cost (saving) per person seen by the OPEN AOS model.

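### The return outcome counts only ED visits, so a renewed emergency episode handled again by OPEN AOS scores as no return; this is sound as a measure of ED use but not as a comparison of safety

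*Protocol article*

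**What the plan says.** All references are to the Protocol article.

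- **Outcome.** Study design lists, among the Component 1 secondary outcomes, "ED re-presentation for any cause within 48 h and 28 days of discharge". Under Component 1, Data analysis, it is to be modelled by logistic regression if events are sufficient. No other return outcome is compared between groups.
- **Nature of the service.** "The OPEN AOS model provides emergency substitution care to older adults residing in RACFs located within the MNHHS catchment area".
- **Repeat treatment.** Under Inclusion criteria, for the intervention group: "Patients can receive treatment by OPEN AOS on more than one occasion within the study period".
- **Repeat contacts in the analysis.** Component 1, Data analysis: "Re-presentations by patients in either group are not considered as independent events and will be excluded from analyses". Only a tally of them over the year is kept, and only for the intervention group. No 48 h or 28-day window is attached to that count, and there is no matching count for controls.
- **Exclusion 6.** "Patients included in the intervention group, i.e. those seen by OPEN AOS will be excluded from the control group". No time limit relative to the control's index episode is given.
- **Data windows (Table 1).** EDIS runs to 28 Jul 2023, which gives 28 days after the last index date. The RADAR Registry, the source of OPEN AOS activity, stops on 30 Jun 2023.
- **Economic model.** Component 2 compares costs "taking into consideration the subsequent probability of presentation and re-presentation to the ED", and its Data analysis takes ED re-presentation from Component 1.

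**The concern.** The same clinical event can be scored differently by group. A control who deteriorates on day 10 and goes back to an ED is a re-presentation. An OPEN AOS patient who deteriorates on day 10 and is managed again by OPEN AOS in the facility is not, although the service exists to replace that ED visit. The unwindowed count of repeat contacts does not repair the comparison.

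The study aims to compare effectiveness and safety. Death and clinical incidents are followed for 48 h only, so re-presentation is the one comparison bearing on safety that reaches 28 days. If it is read that way, the intervention can improve its own result by absorbing returns, with no difference in how often patients need emergency care again. The ED re-presentation figures also feed Component 2.

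**Working it through.** **The plan's own figure.** The article gives no rate or power for re-presentation. Its sample size concerns the primary outcome: with d = 0.2, two-sided 5%, 90% power and 1:3 allocation, n = (1.960 + 1.282)² × (1 + 1/3) / 0.2² = 350.2, so 351 and 1053, as stated. These sizes are used below only as a scale.

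**Set-up (all three quantities are assumptions; the documents give none).**
- R: true 28-day risk of needing emergency care again, equal in both groups.
- f: share of intervention returns handled by OPEN AOS without an ED visit.
- c: share of returning controls seen by OPEN AOS and so removed under exclusion 6.

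**Formulas.**
- Observed intervention rate = R(1 − f).
- Observed control rate = R(1 − c)/(1 − Rc), because removed controls leave both numerator and denominator.
- z = difference / √[p(1 − p)(1/n₁ + 1/n₂)], with p the pooled proportion.

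**Worked case, R = 25%, f = 20%.** Intervention: 0.25 × 0.80 = 20.0%.
- c = 0: control 25.0%. At 351/1053, p = 0.2375, SE = 0.0262, z = 0.050/0.0262 = 1.9.
- c = 20%: control 0.25 × 0.80/(1 − 0.05) = 21.1%. p = 0.208, SE = 0.0250, z = 0.0105/0.0250 = 0.4.

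**Range at R = 25%** (2205 = 3 × 735):

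| f | c | Intervention | Control | z, 351/1053 | z, 735/2205 |
|---|---|---|---|---|---|
| 20% | 0 | 20.0% | 25.0% | 1.9 | 2.8 |
| 20% | 10% | 20.0% | 23.1% | 1.2 | 1.7 |
| 20% | 20% | 20.0% | 21.1% | 0.4 | 0.6 |
| 30% | 0 | 17.5% | 25.0% | 2.9 | 4.2 |
| 30% | 10% | 17.5% | 23.1% | 2.2 | 3.2 |
| 30% | 30% | 17.5% | 18.9% | 0.6 | 0.9 |

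The 735 is an upper bound: the article does not say whether it is counted after removing referrals from outside the ambulance service.

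**Wider range.** For R from 10% to 30% and f from 10% to 50%, the spurious difference runs from −1 to −15 percentage points with c = 0, and from −0.1 to −2.6 points with c = f.

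**Direction.** The net bias favours OPEN AOS when f exceeds c(1 − R)/(1 − Rc). With R = 25% and c = 20% that is 0.15/0.95 = 15.8%. So it favours OPEN AOS whenever its own patients return through it at least as often as controls do, which is plausible but also an assumption.

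**A composite outcome with exclusion 6 left as it is.** Counting ED or OPEN AOS returns gives 25.0% in the intervention group. Controls who returned through OPEN AOS would still be deleted, leaving 21.1% at c = 20%. The bias would then run against OPEN AOS, so the outcome and the exclusion have to be changed together.

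**The case against.** The strongest reply is that the outcome is named for what it measures. Reducing avoidable transports to ED is a stated aim of the service, so a return managed in the facility is a real difference in ED use. That stands: the fault lies in reading the outcome as safety or need for care, not in reporting it.

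Several stronger readings are tempting but unsupported:

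- **The risk ratio is biased to 1 − f.** A reader might infer this because exclusion 6 leaves uncounted OPEN AOS returns in the intervention group alone. But the same exclusion deletes returning controls, who live in the same catchment, and so lowers the control rate. The 1 − f result is the c = 0 extreme.
- **A spurious significant benefit is likely.** No document gives R, f or c, and significance depends on all three. OPEN AOS also works only 08:00–20:00 and triages each referral, so many returns may still reach an ED.
- **Repeat OPEN AOS visits are free in Component 2.** Staffing and non-staffing costs of the model are included, and total annual cost rests on forecast utilisation, so repeat visits may already be paid for. What is not stated is a probability of a repeat OPEN AOS episode.
- **Re-presentations vanish from the analysis altogether.** The exclusion sentence is better read as barring repeat visits as new independent episodes, since logistic regression of ED re-presentation is planned alongside it.

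Additional file 2, which holds the detailed outcome definitions, is not shown and could add to the definition in the article. The RADAR cut-off shortens follow-up only for index episodes discharged in June 2023.

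**Conclusion.** The point holds in limited form. As defined in the article, a renewed emergency episode handled only by OPEN AOS is a non-event in the sole between-group return outcome, and the unwindowed count for one group does not correct this. As a measure of ED use the outcome is sound. As a comparison of safety or renewed need, it tends to favour OPEN AOS.

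The size cannot be derived from the documents. With an assumed equal risk of 25% and 20% of intervention returns absorbed by OPEN AOS, the apparent difference is 5.0 points if exclusion 6 removes no returning controls and about 1.1 points if it removes 20% of them. A false significant finding is possible, not shown. The primary outcome and its sample size are unaffected. Should-fix, secondary outcome.

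**What to change.** 1. Keep ED re-presentation, labelled as a utilisation outcome. Add, in both groups, any unplanned ED presentation or new OPEN AOS episode within 48 h and 28 days of index discharge.
2. Limit exclusion 6 to OPEN AOS contact before or at the control's index episode, so that no control is removed because of a later return through OPEN AOS. State how a resident who then qualifies for both groups is handled, for example by assigning group at the first qualifying episode.
3. Extend the RADAR extract to 28 Jul 2023 to match EDIS.
4. In Component 2, state the probability of a repeat OPEN AOS episode within 28 days and cost it per episode, unless the per-patient service cost already includes repeat visits; if it does, say so.

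The cost is small: outcome and exclusion wording, 28 more days from a registry already being linked, and at most one extra model branch. The downside is that the OPEN AOS return figure may look less favourable.

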However, the coordination and continuity of care for the older adult remains paramount [28, 29]. There are key considerations when providing acute care to an individual in the RACF such as: ascertaining their goals of care; treatment beneficence; non-maleficence (e.g. avoiding futile treatment); and understanding the capacity to diagnose and manage care safely in the home [30]. Various medical problems can be effectively treated and managed in the resident’s home such as urinary tract infections and falls with minor injuries including skin tears or simple lacerations [31]. A recent systematic review of ED transfers determined up to 55% were potentially avoidable, meaning the resident was safe to remain in their home utilising alternative care pathways [32]. Additionally, some evidence suggests that RACF residents and their families have a general preference for treatment to be provided in their home environment [33].

A systematic review of 15 observational studies evaluating acute outreach models of care to people living in RACFs on ED transfer prevention, hospitalisation, safety, cost-effectiveness and experiences [34] highlighted the absence of evidence. The authors recommended that future cluster-randomised or quasi-experimental studies be undertaken to assess the effectiveness and safety of these new outreach models [34].

To support the provision of emergency care for residents in RACFs in Queensland Australia, a novel acute ED substitution outreach model called OPEN AOS (Older Persons Emergency Network Acute Outreach Service) was established. The overarching aim of this study is to evaluate the implementation and outcomes of this ED outreach model. This paper describes the protocol for the evaluation of the OPEN AOS model.

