## Methods

### Study aims

The aims of the OPEN AOS model evaluation are to:

Describe and compare the effectiveness and safety of the OPEN AOS model with standard ambulance attendance resulting in transport to ED care (standard care).Conduct an economic evaluation of the OPEN AOS model; and.Explore and understand the contextual factors influencing implementation to inform delivery and support potential scale and spread of the OPEN AOS model.

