### Data collection and linkage

Patients living in RACFs are identified upon arrival to ED within EDIS^®^ and recorded as arriving by ambulance from a nursing home. Data extraction will occur retrospectively from state-based and MNHHS databases. An anonymous unique identifier (linkage ID) will be assigned to all cases by the Queensland Health Statistical Service Branch (SSB), enabling linkage of data from all sources (Table 1). These data provided to the researchers will not contain any key patient identifying features such as Unit Record Number (URN), name, address or Date of Birth (DOB). However, data such as age, postcode, and health facility will be included in the collection.

**Table 1 Tab1:** Data sources, date ranges and data descriptions for the OPEN AOS evaluation study

Data Source	Time Period	Data Description
RADAR Registry	1 Jul 2022 to 30 Jun 2023	OPEN AOS activity plus outcome data including: • outcomes of intervention • time stamps • clinician delegation Patient demographics for matching variables
Emergency Department Information System (EDIS^®^)	1 Jul 2022 to 28 Jul 2023	ED presentations of cohort members at one of the participating hospitals. • outcomes of intervention • time stamps Patient demographics and RACF address (presentation postcode and suburb) for matching variables
Metro North Health Funding and Data Insights	1 Jul 22 to 28 Jul 2023	Costs of initial ED presentations and subsequent re-presentations within 48 h and 28 days Patient unit record number for matching variables
Queensland Hospital Admitted Patient Data Collection	1 Jul 2020 to 30 Jun 2023	Patient co-morbidities identified during any hospital admission (using ICD-10-AM codes and ICD-10-AM code chapters), during the 24-month period preceding their presentations to the ED Patient demographics for matching variables
Death Registrations from the Registry of Births, Deaths and Marriages Queensland Cause of Death Unit Record File from the Australian Coordinating Registry	1 Jul 2022 to 02 Jul 2023	Death within 48 h of discharge from either emergency department presentation or OPEN AOS intervention Patient demographics for matching variables
RiskMan Queensland Health’s system for recording and managing clinical incidents, workplace events, consumer feedback, and risk	1 Jul 2022 to 02 Jul 2023	Patient Clinical Incident data within 48 h of discharge from the ED Patient demographics for matching variables

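### The 48 h death comparison cannot separate a safety effect from a difference in end-of-life mix, and the direction of the resulting bias is not settled

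*Protocol article*

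**What the plan says.** The first aim (Study aims) is to "Describe and compare the effectiveness and safety of the OPEN AOS model with standard ambulance attendance" ending in ED transport. Among the secondary outcomes in Study design is "Death within 48 h of discharge". Table 1 (Data collection and linkage) describes it for both groups as "Death within 48 h of discharge from either emergency department presentation or OPEN AOS intervention". Neither place divides expected from unexpected deaths. Table 1 also lists the "Cause of Death Unit Record File from the Australian Coordinating Registry", but the article states no use of it to classify deaths.

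The following parts of the plan could control for end-of-life status:

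- **Matching (Samples):** age within 5 years, sex, and ICD-10-AM section or chapter.
- **Exclusions (Exclusion criteria):** six items, none about palliative or end-of-life status.
- **Model (Component 1, Data analysis):** "ED re-presentation and mortality will be examined using logistic regression if there are sufficient events". All regression models carry "fixed effects for triage score, weekend presentation, season, and ambulance referral time". The Charlson index enters only if missing data permit.

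Two statements bear on who enters each group. Under Inclusion criteria, every control was transported to a district ED. Under Intervention: the OPEN AOS model, an OPEN AOS clinician triages each referral and decides whether it is suitable. The Background names, among the considerations for acute care in the facility, "ascertaining their goals of care; treatment beneficence; non-maleficence (e.g. avoiding futile treatment").

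**The concern.** A death in a resident already at the end of life says little about the safety of the care pathway. If such residents form a larger share of one group, that group will show more deaths within 48 h even when the two pathways are equally safe.

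The protocol's own structure makes unequal shares plausible. A resident whose goals of care rule out transport can be an OPEN AOS patient but cannot be a control. Conversely, clinician triage for suitability could keep dying residents out of OPEN AOS. Nothing listed for matching or adjustment would reveal either pattern. The Charlson index counts comorbidity, not goals of care, and a diagnosis section such as infection or injury holds both comfort-care and actively treated residents.

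Death is the most objective of the safety outcomes. An excess under OPEN AOS could arise without harm, and real harm could be hidden. If no rule is fixed beforehand, an observed excess could also be explained away later as palliative.

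**Working it through.** **The plan's own figure.** The article gives no rate, effect size or power for death. Its only sample-size figure is for time to be seen: 351 and 1053 patients, d = 0.2, two-sided 5%. The noncentrality is 0.2/√(1/351 + 1/1053) = 3.245, and 3.245 − 1.96 = 1.285, which gives a power of 90.1% (90.0% by the noncentral t). The figure reproduces. The group sizes are used below only to turn risks into expected deaths.

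**Model for the bias.** Let e be a group's end-of-life share, q the 48 h death risk in end-of-life residents and b the risk in everyone else. Both q and b are the same in the two groups, so there is no true effect. Then

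p = q·e + b·(1 − e), and p(OPEN AOS) − p(control) = (q − b)·(e(OPEN AOS) − e(control)).

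Since q exceeds b, the sign of the bias depends only on which group has the larger share.

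**Inputs.** All rates are assumptions, because the documents give none: q = 30%, b = 1%, with shares varied in both directions.

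- Share 5%: 0.05 × 0.30 + 0.95 × 0.01 = 0.0245
- Share 2%: 0.02 × 0.30 + 0.98 × 0.01 = 0.0158
- Share 3%: 0.03 × 0.30 + 0.97 × 0.01 = 0.0187
- Share 8%: 0.08 × 0.30 + 0.92 × 0.01 = 0.0332

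| Share, OPEN AOS vs control | 48 h risk | Risk ratio | Expected deaths of 351 vs 1053 |
|---|---|---|---|
| 8% vs 2% | 3.32% vs 1.58% | 2.10 | 11.7 vs 16.6 |
| 5% vs 2% | 2.45% vs 1.58% | 1.55 | 8.6 vs 16.6 |
| 3% vs 2% | 1.87% vs 1.58% | 1.18 | 6.6 vs 16.6 |
| 2% vs 2% | 1.58% vs 1.58% | 1.00 | 5.5 vs 16.6 |
| 2% vs 5% | 1.58% vs 2.45% | 0.64 | 5.5 vs 25.8 |

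**Sensitivity to the assumed rates.** With b from 0.5% to 1% and q from 20% to 40%:

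- 5% vs 2% gives an odds ratio of 1.42 to 1.94. With 351 and 1053 patients there is a 13% to 36% chance of a significant excess under OPEN AOS. With all 735 treated patients and 3 × 735 = 2205 controls the chance is 21% to 59%.
- 2% vs 5% gives an odds ratio of 0.51 to 0.70, with an 8% to 23% chance of a significant deficit at 351 and 1053.
- Equal shares of 2% give 1.00.

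**What adjustment would remain.** At 5% vs 2% the expected total is about 25 deaths (8.6 + 16.6). Logistic regression is conditional on sufficient events. If it is dropped, the only other stated methods for a categorical outcome are the unadjusted chi-squared and Fisher tests, so even the listed covariates would not be applied.

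**Is there data for a flag?** Table 1 lists "Patient co-morbidities identified during any hospital admission (using ICD-10-AM codes and ICD-10-AM code chapters") over the 24 months before presentation, extracted from 1 July 2020. The earliest index date is 1 July 2022, so the calendar range reaches back 24 months for every index episode. However, the look-back is worded relative to ED presentations, and an OPEN AOS patient who is not transported has no index ED presentation.

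**The case against.** A reader might infer that OPEN AOS deliberately keeps dying residents in place for comfort care and will therefore look harmful. The documents do not support that. They describe OPEN AOS patients as having acute illness or injury and the service as a substitute for emergency care. The text on goals of care is general background. Only ambulance referrals enter the intervention group, so residents cared for in place without an ambulance call appear in neither group. Triage for suitability could as easily leave fewer dying residents under OPEN AOS. This part of the objection stands: the mechanism is an inference and its direction is open.

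Other points have partial force. Exact matching on diagnosis may remove some of any imbalance. The cause-of-death file could help to characterise deaths. Additional file 2, which is not shown, may define the outcome more closely. The Limitations section concedes selection bias and unmeasured confounding. Yet that concession is generic and leads to no analysis, the article states no use of the cause-of-death file for this purpose, and it fixes the covariates for all regression models without one for end-of-life status.

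The strongest objection is to the remedy. A flag that needs a prior admission may miss residents whose care is directed away from hospital, possibly unequally between groups. Resting the safety conclusion on unflagged patients could keep the bias while demoting the most objective measure. That also stands, and it is why all-cause death should remain the lead result.

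**Conclusion.** The point holds as one of uncontrolled confounding of unknown direction, not as a predicted bias against OPEN AOS. As written, the 48 h death comparison is all-cause, and nothing in the stated matching, exclusions or covariates identifies end-of-life status. Under the assumed risks of 30% and 1%, a difference of three percentage points in end-of-life share moves the risk ratio from 1.00 to 1.55 or to about 0.64 with no true effect. The size rests entirely on assumed rates and shares, and is zero if the shares are equal. The plan should be changed, because the outcome serves a stated safety aim and the repair is cheap. It is a secondary outcome, so the primary analysis is unaffected.

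**What to change.** 1. Keep all-cause death within 48 h as the lead safety result.
2. Pre-specify a pre-index palliative-care flag from the ICD-10-AM codes in the Queensland Hospital Admitted Patient Data Collection, with the same source and the same 24-month window before the index episode in both groups. First confirm that the look-back covers OPEN AOS episodes without an ED presentation and that palliative-care codes are in the extract.
3. Report the flag's frequency by group, and report 48 h deaths with and without the flag as a pre-specified sensitivity analysis. Use the cause-of-death file as descriptive support only.
4. Add the flag to any mortality model if the number of events allows.
5. State that residual confounding by end-of-life status remains, and that its direction is unknown.

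The cost is one derived variable from a source already requested, a few table rows and possibly a clarification of the linkage request. The downside is incomplete capture: residents with no admission in the previous 24 months cannot be flagged, and with few deaths the strata will be small. The stratified figures are therefore for interpretation and not for a separate test.
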